### Sample size

The clinical cure rates for short- and standard-course therapies were estimated using our retrospective dataset. According to a dataset of 361 patients that closely matched the control group in this trial, the clinical cure rate was 95.1% (135/142) in the short-course therapy group and 95.0% (208/219) in the standard-course therapy group, with an overall rate of 95.0% (343/361). This is consistent with the results reported in the literature (46,47). Therefore, a clinical cure rate of 95% was used in both groups for sample size calculation in this trial. The number of patients required for analysis was determined to be 200, with 100 cases per group, assuming a one-sided significance level of 2.5%, power of 90%, and a non-inferiority margin of 10% (39). Anticipating loss to follow-up and other contingencies, the target enrollment was set at 210, with 105 cases per group.

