**Methods:**

We designed a multicenter, non-blinded, randomized trial to evaluate the efficacy of short-course therapy compared to standard-course therapy for AC management. The short-course therapy group will receive 1–3 days of intravenous (IV) antibiotic treatment after successful biliary drainage compared to 4–7 days of IV antibiotics after successful biliary drainage for the standard-course therapy group. The primary outcome is the clinical cure rate within 14 days from the endoscopic retrograde cholangiopancreatography (ERCP) procedure. Participants will be allocated to either treatment course using a minimization method in a non-blinded, randomized manner, with stratification factors including condition severity and facility. We determined that 210 participants would be required to achieve a statistical power of 90% with a one-sided significance threshold of 2.5% and a non-inferiority limit of 10%.

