### Randomization and allocation concealment

Participants in the study will be assigned to one of the treatment groups in a balanced 1:1 ratio within 24 h of the successful completion of biliary drainage. The allocation process will utilize a stochastic minimization method centrally managed by the study’s primary center at the Department of Gastroenterology, Shonan Kamakura General Hospital. A specialized electronic data capture system will be used for randomization and data collection. Stratification factors will include condition severity and facility as criteria.

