Continuous variables will be reported as medians with interquartile ranges, and categorical variables will be reported as numbers with percentages. Continuous and categorical variables will be compared using the Mann–Whitney *U* and chi-square tests, respectively. Risk differences with 95% confidence intervals (CIs) will be calculated for binary outcomes, and the two-sided significance level for all tests will be set at *p* < 0.05. All statistical analyses will be performed using EZR (Saitama Medical Center, Jichi Medical University, Saitama, Japan), a graphical user interface for R version 4.2.3 (R Foundation for Statistical Computing, Vienna, Austria), which is a modified version of the R commander designed to include additional biostatistical functions (48).

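### The stated 90% power and one-sided 2.5% error are not both achieved at 100 per arm by any of the risk-difference intervals checked; an interval that holds 2.5% near the planning rates has about 83% power

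*Protocol article*

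**What the plan says.** The Sample size section of the protocol article takes equal cure rates: "a clinical cure rate of 95% was used in both groups for sample size calculation in this trial". It then fixes the operating characteristics, "assuming a one-sided significance level of 2.5%, power of 90%, and a non-inferiority margin of 10" percent, and the resulting number: "The number of patients required for analysis was determined to be 200, with 100 cases per group". To allow for losses, "the target enrollment was set at 210, with 105 cases per group". Allocation is 1:1 (Randomization and allocation concealment).

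The Methods paragraph of the abstract attaches the same power and error to the enrolled number: "210 participants would be required to achieve a statistical power of 90% with a one-sided significance threshold of 2.5" percent.

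For the analysis, the Statistical analysis section compares cure rates in the full analysis set using 95% confidence intervals and adds: "Risk differences with 95% confidence intervals (CIs) will be calculated for binary outcomes". It names neither the sample size formula nor the interval method.

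**The concern.** At 95% cure, 100 patients per arm yield about 5 failures per arm (100 × 0.05). A normal approximation to a risk difference is weak with so few events, so power and error should be checked against the binomial distribution before both are quoted as properties of the design.

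Two risks are at stake. If the interval used exceeds 2.5% one-sided error, short-course therapy could be declared non-inferior too easily. If it holds 2.5%, the chance of missing true non-inferiority is larger than the planned 10%. The second risk matters here because the Discussion says that a failure to show non-inferiority will be read as support for keeping the current standard duration. Results near the margin can also turn on the choice of interval.

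**Working it through.** **Inputs.** All are from the Sample size section: cure 0.95 in both arms, margin 0.10 on the absolute difference, one-sided error 0.025, power 0.90, 100 per arm analysed, 105 per arm enrolled.

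**1. Reproduce the planned number.** Unpooled normal approximation:

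n per arm = (1.960 + 1.282)² × (2 × 0.95 × 0.05) / 0.10² = 99.8, so 100.

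By the same approximation, power at 100 per arm is 90.05%. A continuity-corrected formula gives 119 per arm and the Farrington-Manning formula about 129. Of the formulas tried, only the simple one returns 100. That the plan used it is therefore an inference from the match.

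**2. Exact operating characteristics.** Let x and y be the numbers cured in the short-course and standard-course arms, and L(x, y) the lower limit of the two-sided 95% interval for short minus standard. Non-inferiority is declared if L > −0.10. Then

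P(declare) = Σₓ Σᵧ Bin(x; n, p_short) × Bin(y; n, p_std) × 1[L(x, y) > −0.10].

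Power is taken at 0.95/0.95. Error is taken on the margin, at 0.85 (short) versus 0.95 (standard).

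| Interval | Power, 100 per arm | Error, 100 per arm | Power, 105 per arm | Error, 105 per arm |
|---|---|---|---|---|
| Wald | 88.6% | 3.39% | 90.0% | 3.24% |
| Agresti-Caffo | 87.4% | 2.82% | 88.9% | 2.72% |
| Newcombe | 83.2% | 2.31% | 85.0% | 2.46% |
| Miettinen-Nurminen | 83.2% | 2.31% | 84.8% | 2.18% |
| Wald, continuity-corrected | 82.7% | 1.78% | – | 1.78% |

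No row has both power of at least 90% and error of at most 2.5%, at either size.

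**3. How far the error statement holds.** At 100 per arm, Newcombe and Miettinen-Nurminen have a maximum error of 2.48% for standard-arm cure rates from 90% to 99%. Over the whole null space they reach 2.78%, at a standard-arm rate of about 55%, far from this trial. At 105 per arm, Miettinen-Nurminen peaks at 2.43% between 90% and 99%, whereas Newcombe reaches 2.62%. Wald error at 100 per arm runs from 3.1% at a 93% standard-arm rate to 3.6% at 97%. An exact unconditional test gives 81.1% power with 2.15% error at 85% versus 95%.

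**4. A result near the margin.** Take 8 failures of 100 on short course and 5 of 100 on standard course, a difference of −3 points. Wald: standard error = √(0.92 × 0.08/100 + 0.95 × 0.05/100) = 0.0348, and the lower limit is −0.03 − 1.96 × 0.0348 = −9.8 points, which passes. The Newcombe lower limit is −10.6 points, which fails. Miettinen-Nurminen also fails.

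**5. What 90% would need.** Exact power with score-type intervals reaches 90% at roughly 120 to 124 per arm (Newcombe 90.6% at 121; Farrington-Manning 90.05% at 124).

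**The case against.** The strongest reply is that nothing has been miscalculated. The number follows from a standard formula, planning on a normal approximation is conventional, and the article does not claim exact power. With the matching Wald interval, exact power is 88.6%, within 1.4 points of the stated figure, and at the 210 quoted in the abstract it is 90.0%. All of this stands. A reader might infer that the sample size calculation is wrong; the documents do not support that.

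A second reply is that the interval is ordinary content for an analysis plan that is not shown. This also stands as far as it goes: the silence is no fault, and neither the 3.4% error nor the shortfall to 83% can be pinned on this trial as a fact. It does not rescue the stated pair, because among the intervals checked the choice only decides which property falls short, and with Agresti-Caffo both do.

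A reader might also infer a strict choice between an error rate about a third too high (3.39/2.5 = 1.36) and power about 7 points too low. That is too stark. Agresti-Caffo lies between, at 87.4% power and 2.8% error. Nor do score-type intervals hold 2.5% everywhere; the claim is limited to cure rates near those planned.

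**Conclusion.** The point holds in a limited form. The planned number is a correct use of a standard approximation, but 90% power together with one-sided 2.5% error is not delivered by any interval examined. With an interval that keeps 2.5% near the planning rates, power is about 83% for 200 analysed and about 85% if all 210 are analysed. The chance of missing true non-inferiority is then about 17% (100 − 83.2 = 16.8), against the planned 10%.

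This rests on the plan's own 95% cure in both arms, equal arm sizes, an unstratified interval, and a decision based on the lower 95% limit against −10 points. It shows a misstated pair of design properties. It does not show an invalid design or a need for more patients.

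**What to change.** Before analysis, name one score-type interval as primary for the non-inferiority decision. Unstratified Miettinen-Nurminen is suitable, since its error stays at or below 2.5% for standard-arm cure rates of 90% to 97% at both 100 and 105 per arm. If the unseen analysis plan already names such an interval, only the power statement needs changing.

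Restate power in the abstract (Methods) and the Sample size section as about 83% for 200 analysed and about 85% if all 210 are analysed. All these figures are for unstratified intervals, so if a stratified interval is preferred, compute its power before stating it.

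The sample size need not change. The cost is some wording and a less favourable stated power. Should the sponsor wish to keep 90% power with a score-type interval, roughly 120 to 124 analysed per arm would be needed.

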### Statistical analysis

Regarding the primary endpoint, the clinical cure rate with 95% confidence intervals will be compared between the short-course therapy group (24–72 h) and the standard-course therapy group (96–168 h) in the full analysis set (FAS), which will include all registered participants who receive any part of the treatment protocol. Subgroup analyses will be conducted based on severity, age, AC etiology, and other baseline factors using the confidence intervals of the differences and logistic regression models. Interaction effects will be examined. The primary analysis population is the FAS; however, analyses using the per-protocol set (PPS), which includes participants from the FAS who had no study protocol violations and were compliant with the protocol, will also be conducted to confirm that the same conclusions are drawn from both sets.

Secondary endpoints will also be examined in both the FAS and PPS sets; these will include the following variables within 30 days: the recurrence and mortality rates, required days of antibiotic use, required days of hospitalization, and treatment costs.

A safety analysis will be conducted among the participants who received the study treatment at least once. All adverse events will be reported, and serious adverse events (SAE) will be tallied separately. Adverse events observed after administration of the trial drug will be tabulated by group, and the number of occurrences, cases, and incidence rates will be calculated and compared between groups. All adverse events will be analyzed, regardless of causality. Descriptive statistics will be calculated by group for clinical laboratory tests, and clinically significant differences will be highlighted. Other parameters will be analyzed by variable type; descriptive statistics will be calculated for continuous variables and frequencies tallied for categorical variables in each group.

Continuous variables will be reported as medians with interquartile ranges, and categorical variables will be reported as numbers with percentages. Continuous and categorical variables will be compared using the Mann–Whitney *U* and chi-square tests, respectively. Risk differences with 95% confidence intervals (CIs) will be calculated for binary outcomes, and the two-sided significance level for all tests will be set at *p* < 0.05. All statistical analyses will be performed using EZR (Saitama Medical Center, Jichi Medical University, Saitama, Japan), a graphical user interface for R version 4.2.3 (R Foundation for Statistical Computing, Vienna, Austria), which is a modified version of the R commander designed to include additional biostatistical functions (48).

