## Background

The risk of developing resistant organisms increases with each additional day of antimicrobial therapy (1). Furthermore, prolonged antibiotic use has been reported to increase healthcare costs; escalate adverse events associated with antimicrobial therapy—such as *Clostridioides difficile* enteritis, invasive candidiasis, antibiotic-induced organ damage; and increase mortality rates in certain infections, including intra-abdominal infections (1–7). Therefore, optimizing antibiotic use in acute cholangitis (AC), which ranks as the second or fourth most prevalent cause of community-acquired bacteremia (8,9), is crucial for suppressing resistant bacteria and reducing antibiotic-associated adverse events (10).

The Tokyo Guidelines 2018 (TG18), a well-recognized set of guidelines for AC management, recommend antibiotic therapy and biliary drainage as the primary treatment modalities. TG18 suggests a standard duration of 4–7 days for antibiotic administration post-biliary drainage (11). However, it is noted that a duration of ≤ 3 days of antimicrobial therapy may suppress the development of resistant organisms (12).

A recent randomized controlled trial (RCT) compared 4- and 8-day antibiotic treatment durations and confirmed the non-inferiority of the shorter regimen (13). Additionally, recent retrospective studies have suggested that an even shorter course of antibiotics, lasting 1–3 days post-biliary drainage, may be effective in treating AC (14–16). These studies indicate that reducing the duration of antibiotic therapy does not compromise the clinical cure rate and may mitigate the risks associated with prolonged antibiotic use, including the development of resistant organisms and other adverse effects.

Despite the growing body of evidence, recommendations are predominantly based on small retrospective studies. Therefore, obtaining more robust evidence to refine and validate the optimal antibiotic therapy duration for AC is imperative to ensure maximal therapeutic benefit while minimizing adverse effects. This study aims to evaluate whether short-course therapy is non-inferior to standard-course therapy in terms of clinical cure rate. The research is crucial for developing evidence-based guidelines that balance the efficacy of treating AC with the need to prevent the emergence of resistant bacteria and reduce antibiotic-related adverse events.

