### Outcome measures

The primary outcome was defined as the rate of cases that achieved clinical cure within 14 days and survived without recurrence, according to the guidelines recommended by the U.S. Food and Drug Administration for complicated urinary tract infection outcomes (39). Clinical cure refers to the resolution of all pre-treatment clinical symptoms (chills, fever > 37.5 °C, abdominal pain, jaundice, impaired consciousness). Recurrence was defined as the reappearance of clinical signs suggestive of cholangitis in a case that had completed antibiotic therapy and achieved clinical cure, necessitating the resumption of antibiotic administration. Clinical signs suggestive of cholangitis recurrence include any of the following: (1) reappearance of clinical signs of cholangitis; (2) manifestation of signs of infection in the liver, pancreas, or biliary tract; or (3) other signs of infection considered related to the initial cholangitis episode (30,40).

The secondary outcomes include the following:Recurrence rate within 30 daysMortality rate within 30 daysTotal number of days of antibiotics required for both groups within 30 daysTotal number of days of hospitalization required for both groups within 30 daysClinical cure rates by severityClinical cure rates by the presence or absence of fever at the end of antibiotic treatmentClinical cure rates in older populations aged ≥ 75 years (18,41)Clinical cure rates by blood culture resultsClinical cure rates by bile culture resultsClinical cure rates based on antibiotic susceptibility before ERCPClinical cure rates based on antibiotic administration duration before ERCPClinical cure rates based on the time from admission to the ERCP procedureClinical cure rates based on AC etiologyTreatment costsIncidence of the following adverse events within 14 days:(a). Rash(b). Diarrhea (defined as ≥ 3 loose stools per day (42))(c). *C. difficile* enteritis (42), confirmed experimentally and through clinical signs

Clinical signs: Presence of diarrhea (≥ 3 formless stools within 24 h).

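### The primary outcome is defined as cure plus survival without recurrence, but the abstract, objective, sample size and analysis name only the clinical cure rate, which the protocol defines as symptom resolution

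*Protocol article*

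**What the plan says.** Three definitions under Outcome measures have to be read together.

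- The primary outcome: "The primary outcome was defined as the rate of cases that achieved clinical cure within 14 days and survived without recurrence".
- One component of it: "Clinical cure refers to the resolution of all pre-treatment clinical symptoms" (chills, fever, abdominal pain, jaundice, impaired consciousness). Neither survival nor absence of relapse is part of this.
- Recurrence: reappearance of signs "in a case that had completed antibiotic therapy and achieved clinical cure, necessitating the resumption of antibiotic administration". A recurrence can therefore occur only in a patient who already counts as clinically cured.

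Elsewhere only the component is named.

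- Abstract, Methods: "The primary outcome is the clinical cure rate within 14 days from the endoscopic retrograde cholangiopancreatography (ERCP) procedure".
- Background, objective: "This study aims to evaluate whether short-course therapy is non-inferior to standard-course therapy in terms of clinical cure rate".
- Sample size: "a clinical cure rate of 95% was used in both groups for sample size calculation in this trial".
- Statistical analysis: "Regarding the primary endpoint, the clinical cure rate with 95% confidence intervals will be compared between the short-course therapy group" and the standard-course group.

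The severity, age, culture and aetiology breakdowns among the secondary outcomes are also labelled clinical cure rates. Recurrence and mortality appear separately, as 30-day secondary outcomes.

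**The concern.** By the protocol's own definitions, a patient whose symptoms resolve on day 3 and who relapses or dies on day 10 is a clinical cure and is also a failure on the primary outcome. The document therefore names two primary variables that classify the same patient differently.

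The direction matters. Relapse after antibiotics stop early is the main harm that a 1–3 day course has to be shown not to cause. A symptom-resolution rate cannot register it once symptoms have cleared. If relapse is more common after the short course, leaving it out shrinks the observed difference and makes a non-inferiority claim easier.

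The setting makes a fixed definition more important. The trial is open-label, attending physicians assess the outcomes, and the Discussion relies on clear outcome definitions to offset that subjectivity. If both readings are still open when the data are analysed, the choice between them could be made with results in view.

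**Working it through.** **1. How each outcome is classified**

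| Course up to day 14 | Clinical cure as defined | Primary outcome as defined |
|---|---|---|
| Resolves, alive, no recurrence | Success | Success |
| Never resolves | Failure | Failure |
| Resolves, then recurs | Success | Failure |
| Resolves, then dies | Success | Failure |

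The two variables differ only in the last two rows.

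**2. The plan's own figure**

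Inputs from Sample size: 95% in both groups, margin 10 points, one-sided 2.5%, power 90%.

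n per group = [p(1−p) + p(1−p)] × (z₀.₉₇₅ + z₀.₉₀)² / margin²

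= 2 × 0.95 × 0.05 × (1.960 + 1.282)² / 0.10² = 99.8, so 100 per group and 200 in total.

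This reproduces the stated number, so the arithmetic is sound. The retrospective rates also check: 135/142 = 95.1%, 208/219 = 95.0%, 343/361 = 95.0%.

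**3. What the choice of variable could do to the conclusion**

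From the plan: 100 per arm, 10-point margin, two-sided 95% confidence interval for the difference.

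Assumed, because the document gives no relapse rate: 95% symptom resolution in both arms, no relapse on standard course, and 5% of all short-course patients resolving and then relapsing by day 14. The composite rates are then 95% − 5% = 90% (short) and 95% − 0% = 95% (standard).

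The probability that the lower confidence limit exceeds −10 points was obtained by summing the two binomial distributions exactly. Two interval methods were used, since the article does not name one.

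| Variable analysed | True rates, short v standard | Newcombe | Wald |
|---|---|---|---|
| Symptom resolution | 95% v 95% | 83.2% | 88.6% |
| Composite | 90% v 95% | 23.2% | 29.8% |

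If the assumed short-course relapse is 10%, the composite rates are 85% v 95% and the true deficit equals the margin. The composite then gives 2.3% (Newcombe) or 3.4% (Wald), while the symptom-resolution row stays at 83–89%.

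**4. What it could do to the planned power**

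Power at 100 per group, using the plan's own approximation, is Φ(0.10 / √(2p(1−p)/100) − 1.960).

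| Composite rate in both arms | Standard error | Power |
|---|---|---|
| 95% | 0.0308 | 90.1% |
| 94% (assumed) | 0.0336 | 84.6% |
| 93% (assumed) | 0.0361 | 79.1% |
| 92% (assumed) | 0.0384 | 74.1% |

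The first row applies if 343/361 already counts relapse and death as failure. The others apply only if 95% is a symptom-resolution rate and a further 1–3% of patients in each arm then relapse or die.

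**The case against.** The strongest reply is that the label is shorthand. Outcome measures is the only section that defines the primary outcome, and it includes survival and recurrence expressly. The analysis sentence begins by referring to the primary endpoint, which points back to that definition. No section says that a relapse or death after resolution counts as a success. This is a plausible reading and it cannot be excluded. A reader might infer that the trial will in fact count relapses as successes; the text permits that but does not establish it. What remains is that clinical cure has its own, narrower definition beside the composite, and nothing says that the short label stands for the longer one.

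A reader might also infer that the primary outcome has no time limit for survival and recurrence, because the 14 days are attached to cure. The documents point to day 14: the abstract sets the outcome at 14 days from ERCP, Assessment and follow-up schedules a day-14 visit, and the 30-day window is given only to secondary outcomes. The sentence should be tightened, but there is no competing horizon.

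A third tempting inference is that the trial is underpowered. Sample size does not say how cure was counted in the retrospective cohort, and 100 per group reproduces at 95%. No power error is shown.

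Two further points are fair. The contrast of 5% with 0% relapse is an assumption, and the retrospective arm rates (95.1% and 95.0%) give it no support, although their definition is unstated. In addition, recurrence and mortality are analysed as secondary outcomes in both analysis sets, so an excess would be visible. It would not, however, enter the test on which non-inferiority is declared.

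**Conclusion.** The point holds as a conflict over what the primary variable is. The defined outcome is a composite; the abstract, objective, sample size and analysis name one component of it. Shorthand is possible but unstated. Read literally, the analysis rule scores a relapse or death after resolution as a success, and where such events are commoner on the short course that biases the comparison towards non-inferiority.

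The size depends on relapse rates that the document does not give. Under the assumed 5% v 0%, the chance of declaring non-inferiority is 83–89% on symptom resolution and 23–30% on the composite. With equal relapse in both arms the two readings would differ much less. The effect on power is conditional on how 343/361 was counted: 90% stands if it was the composite, and about 79% would apply at an assumed composite rate of 93%.

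**What to change.** - Use one primary variable, under one name, in the abstract, the objective, Outcome measures, Sample size and Statistical analysis: all pre-treatment symptoms resolved by day 14 after ERCP, alive at day 14, and no recurrence through day 14.
- Use the same composite for the breakdowns now labelled clinical cure rates, and report symptom resolution alone as a component.
- State which definition the 343/361 rate used. Only if it was symptom resolution alone, recompute the composite rate from that dataset and restate the power at 100 per group.
- Settle this before outcomes are analysed.

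The cost is wording in five sections and, if needed, a recount of a dataset that the sponsor already holds. The change itself needs no new data. The one drawback is that the stated power may come out lower than 90%.

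### Allocation is minimised on severity and facility, but the methods named for the primary comparison carry neither factor; stratifying the risk difference by severity would be a small, nearly free gain

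*Protocol article*

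**What the plan says.** Under 'Randomization and allocation concealment' the protocol article states: "The allocation process will utilize a stochastic minimization method centrally managed by the study’s primary center". It adds: "Stratification factors will include condition severity and facility as criteria". The ratio is 1:1.

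Under 'Statistical analysis' the primary comparison is described as: "the clinical cure rate with 95% confidence intervals will be compared between the short-course therapy group" and the standard-course group, in the full analysis set. The general rules later in that section are chi-square tests for categorical variables and, for binary outcomes, "Risk differences with 95% confidence intervals (CIs) will be calculated for binary outcomes". Logistic regression is named once, for subgroup analyses, and severity is one of those subgroups. Facility has no role in the described analysis.

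Under 'Sample size': "a clinical cure rate of 95% was used in both groups for sample size calculation in this trial". The margin is 10 percentage points, at one-sided 2.5% and 90% power. "The number of patients required for analysis was determined to be 200, with 100 cases per group"; enrolment is set at 210.

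**The concern.** Balancing the arms on a factor that predicts cure removes that factor's contribution to the variance of the difference in cure rates. A crude standard error still counts that contribution, so the interval comes out a little wider than the design warrants. An analysis that carries the balancing factor recovers the difference.

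The non-inferiority conclusion rests on one confidence limit against a 10-point margin, with about 5 expected failures per arm (5% of 100). It is therefore worth settling in advance which estimate supplies that limit. In an open-label trial with so few failures, a choice between a crude and a stratified estimate made after seeing the data could decide a borderline result.

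**Working it through.** **1. The plan's own figure.** Inputs from 'Sample size': cure 0.95 in both arms, margin 0.10, one-sided 2.5%, power 90%.

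n per arm = 2 × 0.95 × 0.05 × (1.960 + 1.282)² / 0.10² = 99.8, so 100. The stated 100 per group reproduces.

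At 100 per arm:
- SE = √(2 × 0.95 × 0.05 / 100) = 0.0308.
- The 95% half-width is 1.96 × 0.0308 = 6.04 points.
- Power = Φ(0.10/0.0308 − 1.960) = 90.05%.

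No adjustment enters this calculation.

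**2. Variance removed by stratifying on severity.** The article gives neither the severity mix nor cure by severity, so both are assumed: three grades in the proportions 40/45/15%.

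Share removed R = 1 − Σ wₖpₖ(1 − pₖ) / [p(1 − p)], where p is the overall cure rate. Effective N = 210/(1 − R). Half-width = 6.04 × √(1 − R).

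| Assumed cure by grade | Σ wₖpₖ(1−pₖ) | p(1−p) | R | Effective N | Half-width, points |
|---|---|---|---|---|---|
| equal | – | – | 0 | 210 | 6.04 |
| 97/95/90% | 0.04652 | 0.04705 | 1.1% | 212 | 6.01 |
| 98/95/87% | 0.04618 | 0.04750 | 2.8% | 216 | 5.96 |
| 99/95/84% | 0.04550 | 0.04795 | 5.1% | 221 | 5.88 |

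**3. Power at the largest of these gains (R = 5.1%, √(1 − R) = 0.974).**
- Stratified: Φ(0.10/(0.0308 × 0.974) − 1.960) = 91.5%.
- Crude interval, with the arms balanced on severity: Φ((0.10/0.0308 − 1.960)/0.974) = 90.6%.

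The gain is about 1.4 points over the planned 90.05%, and about 0.8 points over what the crude interval would deliver. With no severity effect it is zero.

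**4. Does the gain survive with few failures?** Biased-coin minimisation was simulated with 200 patients, 10 facilities, probability 0.8 and 4,000 runs per scenario (all assumed). The crude Wald interval was compared with a Mantel-Haenszel risk difference over severity only.

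| Assumed cure by grade | Half-width, crude to stratified | Power, crude to stratified | Non-inferiority declared at a true 10-point deficit, crude / stratified |
|---|---|---|---|
| 97/95/90% | 5.92 to 5.89 | 90.1% to 90.4% | 2.7% / 2.6% |
| 98/95/87% | 5.95 to 5.87 | 88.5% to 89.2% | 3.2% / 3.2% |
| 99/95/84% | 5.96 to 5.80 | 89.0% to 89.9% | 2.9% / 3.0% |

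A separate simulation of the same stratified estimate gave 3.1–3.5% crude against 3.4–3.7% stratified at that deficit, again with about 1 point or less of extra power. The Monte Carlo error on these percentages is about √(0.03 × 0.97/4000) = 0.27 points.

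Two things follow. The gain is real but small. Both Wald-type intervals tend to run above the nominal 2.5%, and stratifying with a simple within-stratum variance does not cure that.

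**5. Adding facility to the model.** A linear model adjusting for severity and all 10 facilities was simulated under a 40/40/20% mix. With cure 97/95/91% it gained nothing: half-width 5.95 crude against 5.97 adjusted, power 89.1% against 89.0%. With 99/96/85% it moved the half-width from 5.92 to 5.80 and power from 90.2% to 90.9%. About 10 failures are too few to support a term for each site.

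**The case against.** A reader might infer that the protocol prescribes an unadjusted primary analysis. It does not say so. The chi-square and risk-difference sentences are general rules for all variables, no wording excludes stratification, and a full protocol or SAP that is not shown could specify it. That limits the point. The article is nevertheless not silent on method: it names the effect measure, the test, the software and a role for severity, and that role is subgroup analysis.

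The size can also be challenged, and that challenge largely stands. The gain depends on assumed rates. 'Exclusion criteria' removes patients on catecholamines at ERCP, those needing intensive care and those with hypothermia, so a steep severity gradient is less likely and the lower end of the range is more plausible. One patient changing outcome in an arm of 100 moves the difference by 1 point, against at most 6.04 − 5.88 = 0.16 points of half-width gained.

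That adjustment can give no gain at all also stands, but for the model with every facility in it. Stratifying by severity alone gave a small gain in each simulated scenario.

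Finally, stratifying by severity alone does not match the allocation fully. That is accepted, because facility strata would be too sparse to carry the primary estimate.

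**Conclusion.** The point holds as a minor one. The methods named for the primary comparison do not carry the factors used in allocation. If severity is prognostic, the crude interval is on average slightly too wide. Under the assumed mixes the gain from stratifying is 0 to about 5% of variance, or about 0 to 1.5 points of power.

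Stronger readings are not supported. A reader might infer that the trial is underpowered, but the stated 100 per group and 90% power were computed without adjustment and reproduce. A reader might infer an invalid test or an inflated false-positive rate from ignoring the factors; for large samples the theoretical effect is in the conservative direction. Nor can a reader count on that conservatism: with about 10 failures expected, the crude Wald interval declared non-inferiority in 2.7–3.5% of simulated trials at a true 10-point deficit, so small-sample behaviour outweighs it.

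All the gains rest on assumed severity proportions and cure rates, and the simulations also on an assumed number of sites and minimisation probability.

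**What to change.** Before data review, state in the SAP that:
- the primary risk difference is stratified or standardised by the severity grade used in minimisation;
- its 95% interval is of score type, for example stratified Miettinen-Nurminen, rather than a simple within-stratum Wald variance, because so few failures are expected;
- the crude risk difference is reported as supportive;
- facility, with small sites pooled, enters only a sensitivity analysis.

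If the SAP already specifies this, only the published description needs aligning. The cost is a sentence or two of SAP wording and a few lines of R. Both factors are already recorded for allocation, and the sample size does not change.
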